##### Data transformations

2.7.2.4

Data transformations will generally not be performed given the use of a late fusion model, where each individual model is designed to handle different data distributions independently. Exceptions include the binarization of some features with few non-missing values as described above, and a centered-log ratio (CLR) transformation of microbiome features, used to account for the compositionality issue of sequencing data (93).

### Data management

2.8

#### Initial data contribution and management

2.8.1

Data contribution and access for IMiC are illustrated in Figure 3 and governed by data sharing agreements. All PII is removed from the data prior to contribution. Briefly, each study provides its required data for IMiC harmonization (a subset of their entire study dataset) to the Ki team at the Bill & Melinda Gates Foundation via secure upload to their Synapse platform. Similarly, each HM analysis lab securely uploads their data to Synapse, or securely transfers their data to the University of Manitoba for upload to Synapse. Synapse is a secure collaborative compute space that allows scientists to share and analyze data together.^2^ Data housed within the Ki Synapse platform are not available or open to the public.

**Figure 3 fig3:**
[figure not shown]
Data and sample flow for the International Milk Composition (IMiC) Consortium. AL, Academic Labs; BMGF, Bill & Melinda Gates Foundation; CL, Commercial Labs; DSP, Data Science Partners; FS, Field Sites; GHC, Global Health Collaboratory; Ki, Knowledge Integration; UHN, University Health Network; UM, University of Manitoba.

#### Long-term data management

2.8.2

For long-term data management and storage, a bespoke IMiC Database will be developed by the University Health Network and housed within the University of Manitoba’s Secure Research Environment. All final IMiC datasets will be transferred from Synapse to the IMiC Database. Standardized file descriptions and data dictionaries will be used across studies. A user-friendly browser-based interface will enhance accessibility for authorized users. This database will support long-term management and utilization of IMiC data, and can be expanded to integrate similar datasets from future HM studies, offering opportunities for cross-comparison and meta-analysis.

#### Data access and availability

2.8.3

Initially, data access will be managed on the Ki Synapse platform and restricted to IMiC members according to their assigned role. For example, core data analysts require access to all datasets from all studies, while individual study investigators require access only to their own study data and HM data. Following publication of primary IMiC results, the final IMiC dataset will be available for secondary analysis upon request via the IMiC database, in alignment with the parameters of original informed consent of each study.

### Data analysis

2.9

#### Primary exposures and outcomes

2.9.1

The main exposure and outcome variables of interest to IMiC can be structured into categories based on the research questions summarized in Box 1. Our two overarching hypotheses are: (1) maternal and environmental factors (exposures) affect HM composition (outcome), and (2) HM composition (exposure) affects infant growth (outcome). These hypotheses can be explored independently, but we also aim to integrate them, and estimate how various states of maternal nutrition affect the predicted impact of milk composition on infant growth. Overall, maternal nutritional status is an exposure with indicators including maternal anthropometrics (BMI, MUAC) and nutritional interventions. Other exposures for hypothesis 1 include maternal age, parity and indicators of the physical and social environment. HM composition is the outcome for hypothesis 1, but is also the primary exposure for hypothesis 2. Meanwhile, infant growth is the primary outcome of interest, and the main indicators of this will be length for age z-scores (LAZ), weight for age z-scores (WLZ), and weight for length z-scores (WLZ). Given the importance of wasting (WLZ < −2) and stunting (LAZ < −2) as indicators of chronic undernutrition, the prevalence of these conditions at 3, 6, 12, and 18 months of age will also be predicted from integrated-omic models to explore if associations with milk composition differ compared to continuous growth measures.

#### Integrated analysis of HM composition and infant growth

2.9.2

We aim to use an integrative multiomics approach to increase the accuracy of a model predicting infant growth outcomes from HM components, and to identify novel molecular pathways associated with the predicted growth outcomes. A machine learning pipeline developed by the [name] Lab will be used to address this aim and assess whether the integrative multiomics approach increases model accuracy for predicting growth outcomes. A more complete analysis plan is described in the supplement (Supplementary material). Briefly, we will predict infant growth outcomes and baseline risk factors while controlling for potential confounders using algorithms tailored to each modality that implement eXtreme Gradient Boosting (XGBoost) (94, 95). Models will be validated using a customized two-layered cross-validation strategy designed to ensure the models’ robustness and generalizability, assessed using performance metrics such as AUROC, AUPRC, or Spearman’s *ρ*. Key milk components of interest will be identified using a feature selection process that combines forward selection and backward elimination. Further, a late fusion technique will be used to integrate omics modalities and epidemiological data in a combined model. Lastly, pathway enrichment analysis will be conducted to aid in the biological interpretation of predictive models, and to potentially identify molecular mechanisms that underlay the effect of HM components on infant growth.

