**Methods and analysis:**

IMiC is a collaboration of HM experts, data scientists and four mother-infant health studies, each contributing a subset of participants: Canada (CHILD Cohort, *n* = 400), Tanzania (ELICIT Trial, *n* = 200), Pakistan (VITAL-LW Trial, *n* = 150), and Burkina Faso (MISAME-3 Trial, *n* = 290). Altogether IMiC includes 1,946 HM samples across time-points ranging from birth to 5 months. Using HM-validated assays, we are measuring macronutrients, minerals, B-vitamins, fat-soluble vitamins, HM oligosaccharides, selected bioactive proteins, and untargeted metabolites, proteins, and bacteria. Multi-modal machine learning methods (extreme gradient boosting with late fusion and two-layered cross-validation) will be applied to predict infant growth and identify determinants of HM variation. Feature selection and pathway enrichment analyses will identify key HM components and biological pathways, respectively. While participant data (e.g., maternal characteristics, health, household characteristics) will be harmonized across studies to the extent possible, we will also employ a meta-analytic structure approach where HM effects will be estimated separately within each study, and then meta-analyzed across studies.

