BOX 1Research questions addressed in the International Milk Composition (IMiC) Consortium.1) How do the ranges and distributions of nutritive and non-nutritive HM components vary across different geographic settings, including lower-middle resource settings?2) What maternal and environmental factors influence this variation in HM composition? Are these relationships consistent across different settingsh?3) Do maternal nutritional interventions have a direct effect on HM composition?4) How does HM composition and its variation relate to infant growth? Are these relationships consistent across different settings?5) Does HM composition mediate the effect of exogenous factors (e.g., maternal nutrition status or interventions) on infant growth outcomes?6) Are the above relationships consistent at different stages of lactation?7) How do the diverse components of HM correlate with each other? Can we better answer the above questions by taking a systems biology approach to investigating comprehensive HM ‘profiles’ rather than discrete HM components?

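### For non-randomised maternal and environmental factors, the only model the article describes predicts the factor from milk, although hypothesis 1 makes milk the outcome

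*Protocol article*

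**What the plan says.** Section 2.9.1 sets the direction of hypothesis 1: "HM composition is the outcome for hypothesis 1, but is also the primary exposure for hypothesis 2". On the exposure side, "maternal nutritional status is an exposure with indicators including maternal anthropometrics (BMI, MUAC) and nutritional interventions", and the section adds maternal age, parity and the physical and social environment. Box 1 asks: "What maternal and environmental factors influence this variation in HM composition", and whether the relationships are consistent across settings.

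The abstract says the machine learning methods "will be applied to predict infant growth and identify determinants of HM variation". Section 2.9.2 describes that pipeline: "we will predict infant growth outcomes and baseline risk factors while controlling for potential confounders using algorithms tailored to each modality". It uses XGBoost models by modality, joined by late fusion and judged by AUROC, AUPRC or Spearman's correlation. On naming components it says: "Key milk components of interest will be identified using a feature selection process that combines forward selection and backward elimination".

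Two other places bear on the point:
- Section 2.9.3 estimates effects on individual milk components by targeted maximum likelihood with Benjamini-Hochberg correction, but only for the randomised interventions.
- Section 2.7.1.3 plans site-specific analyses and calls caesarean delivery, birth season and maternal BMI exposures, but states no model.

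**The concern.** For the non-randomised factors, the described model has the factor as target and milk as predictor, the reverse of hypothesis 1. Adjusting for confounders does not undo this. The components in one model are themselves possible effects of the factor, so each is judged conditionally on other effects of the same factor.

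Two errors can follow when components are correlated:
- An unaffected component can be selected because it removes noise from an affected one.
- An affected component can be eliminated because another already carries its information.

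The performance measures describe how well milk predicts the factor. They do not say by how much the factor shifts each component, which is what the cross-setting comparison in Box 1 needs. CHILD, with 399 of the 1,039 dyads (Table 3), has no maternal nutritional intervention (Table 4), so Section 2.9.3 contributes nothing there.

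**Working it through.** The article states no figure for this point, so there is none to reproduce. Effect sizes and correlations between components are not given, and those below are assumptions.

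**1. Direction, side by side**

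| Factor | Model described | Direction |
|---|---|---|
| Randomised interventions (2.9.3) | each component as outcome | factor to milk |
| BMI, MUAC, age, parity, environment (2.9.2, abstract) | factor as predicted target | milk to factor |
| Site-specific analyses (2.7.1.3) | none stated | not stated |

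The abstract and Section 2.1 describe the study-by-study meta-analysis for effects of milk, not for effects on milk.

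**2. Why selection and effect differ**

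Let X be the factor (variance 1), M1 = bX + e1 an affected component and M2 = e2 an unaffected one. The residuals have variance 1 and correlation r. Then:

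- corr(X, M1) = b/√(1 + b²)
- corr(X, M2) = 0
- corr(X, M2 given M1) = −br/√(1 + b² − r²)

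With b = 0.5, corr(X, M1) = 0.5/√1.25 = 0.45, and the partial correlation of the unaffected M2 is:

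- r = 0.5: −0.25/√1.00 = −0.25
- r = 0.7: −0.35/√0.76 = −0.40
- r = 0.8: −0.40/√0.61 = −0.51

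With b = 0.1 it is small:

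- r = 0.3: −0.03/√0.92 = −0.03
- r = 0.5: −0.05/√0.76 = −0.06

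**3. Four-component simulation**

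C1 = bX + 0.8U + 0.6e is affected. C2 = 0.8U + 0.6e is unaffected, with residual correlation 0.8² = 0.64 with C1. C3 = C1 + 0.5e is affected through C1. C4 is noise. The factor-as-target analysis uses linear forward/backward selection by BIC. The component-as-outcome analysis uses Benjamini-Hochberg at 5%. Results for b = 0.3 (300 runs; 200 at n = 1,039), at sample sizes from Table 3:

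| n | Factor as target: C2 kept | Factor as target: C3 kept | Component as outcome: C2 flagged | Component as outcome: C3 flagged |
|---|---|---|---|---|
| 150 | 71% | 18% | 3% | 83% |
| 290 | 96% | 9% | 5% | 99% |
| 399 | 99% | 5% | 3% | 100% |
| 1,039 | 100% | 1% | 3.5% | 100% |

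XGBoost with forward/backward selection on cross-validated Spearman correlation (b = 0.4, 25 to 30 runs) kept C2 in 100% of runs at both n = 399 and n = 1,039. It kept C3 in 27% and 12%. The pattern is therefore not peculiar to linear BIC selection.

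**4. Separate modality models**

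With C1 and C2 in different models, C2 was kept in only 0 to 3% of runs. C3 was still dropped in about 83 to 99%.

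**5. Twenty components, equal residual correlation, one linear BIC model**

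| Setting | Runs selecting at least one unaffected component |
|---|---|
| One affected, b = 0.5, r = 0.5–0.7, n = 150–400 | essentially all (component as outcome: 3–7%) |
| One affected, b = 0.2, r = 0.3–0.5, n = 150 | 55–59% |
| One affected, b = 0.1, r = 0.3–0.5 | 24–33% |
| Zero correlation | 37–42% at n = 150; 25–27% at n = 400 |

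The zero-correlation row shows how lenient BIC selection is before direction plays any part. At b = 0.1 the rate does not clearly exceed it. With all 20 components affected by 0.5 SD (r = 0.7, n = 200–400), factor-as-target selection kept about 2 of 20 and the component-as-outcome analysis kept all 20.

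**The case against.** The strongest reply is that Section 2.9.2 is a summary. Its title and stated aim concern infant growth, baseline risk factors appear once, and a fuller plan is in a supplement not shown. The abstract's phrase on determinants fixes no direction. Section 2.7.1.3 treats BMI, birth season and caesarean delivery as exposures, and the secondary mediation analysis for other maternal factors would ordinarily need a factor-to-milk model. Predicting a factor from milk is also a valid global test of association and suits the profile question in Box 1.

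Much of this stands. It does not remove the point, because the article positively describes a model in the opposite direction and gives the pipeline the task of finding determinants. The supplement may hold the right analysis, but the article does not describe it.

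A reader might infer four stronger things that the documents do not support:
- **Hypothesis 1 is analysed backwards as a whole.** It is not: the randomised interventions run in the right direction.
- **All components enter one model.** The text says modality-specific models with late fusion, which limits false selection across modalities. It helps less within one: Table 5 puts 242 triglycerides in one panel and lists HMO totals beside the individual HMOs.
- **False components arise by construction.** They depend on unstated effects and correlations, and part of the simulated rate is lenient selection.
- **The plan will mis-rank determinants.** The article never says it will rank them, and it calls the selected features components of interest, not components a factor affects.

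**Conclusion.** The point holds for the non-randomised maternal and environmental factors. The model described runs opposite to the stated hypothesis, so its selected components should not be read as those the factor changes.

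The size is conditional. Under assumed shifts of 0.3 to 0.5 SD and residual correlations of 0.5 to 0.8, unaffected components in a shared model are usually selected. At 0.1 SD there is no clear excess over chance selection. The loss of redundant affected components is less sensitive to modality structure and persists when modalities are modelled separately. The absence of a per-component effect for comparison across settings needs no numerical assumption, since it follows from the choice of target. The point deserves correction before analysis but does not touch Section 2.9.3 or the prediction of growth.

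**What to change.** For Objective 2, extend the component-as-outcome analysis of Section 2.9.3 to the non-randomised factors. Regress each milk component, and a few profile summaries, on the factor with its confounders and exact day of lactation, within study and by time point. Day matters even within a nominal visit: infant age at collection in CHILD is 115.0 ± 35.2 days (Table 2). Apply Benjamini-Hochberg with the same outcome tiers, then meta-analyse the within-study effects over the studies that measured the factor (maternal MUAC is available in two, Table 3).

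Keep prediction of risk factors from milk as a descriptive or global-association analysis, and state that it will not be used to name the components a factor affects. If the supplement already contains the component-as-outcome analysis, Section 2.9.2 and the abstract need only point to it.

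The cost is plan wording and additional routine regressions on existing data. Residual confounding remains for observational factors and must be acknowledged; Section 2.7.1.3 already notes that confounding of BMI differs between sites.

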#### Intervention effects analysis

2.9.3

We will also estimate the effects of randomized interventions on human milk components in the three intervention studies. Two different definitions of ‘milk composition’ will be used (1) individual milk components, adjusted for multiple testing and (2) predictive summary measures calculated from milk biomarkers of infant growth using targeted learning and other dimension reduction techniques (96). We will estimate both unadjusted and covariate-adjusted intervention effects on each HM outcome, adjusting for baseline prognostic factors using cross-validated targeted maximum likelihood estimation (97). In addition to analyzing HM components at each time point, we will also examine changes in HM components between timepoints. We will correct for multiple comparisons by using the Benjamini-Hochberg procedure, and group corrections by time-point and outcome group. Primary outcomes are macro- and micro-nutrients, secondary outcomes are HMOs and targeted proteins and bioactives, tertiary outcomes are targeted metabolomics, and exploratory outcomes and untargeted metabolomics, untargeted proteomics, and the microbiome.

As a secondary analysis, we plan to assess the potential mediating effects of HM components on the relationship between maternal nutritional supplementation or other maternal factors, and infant growth outcomes (Supplementary material).

### Consortium operations

2.10

#### Guiding principles of collaboration

2.10.1

Data sharing, subawards, and intellectual property ownership are governed by legal agreements between the University of Manitoba, the Bill & Melinda Gates Foundation and other participating institutions. The overall guiding principles of IMiC are outlined in the IMiC Consortium Agreement, a non-legally-binding document that was co-developed by consortium members in order to promote collaboration, transparency and equity among all members. The Consortium Agreement describes the overall goals and vision of IMiC, its governance structure (including an external scientific advisory committee), and its general principles of collaboration, confidentiality, equity, expediency, data stewardship and research integrity. This agreement also outlines policies and expectations related to data sharing and confidentiality, publication and authorship, communications and intellectual property ownership.

#### Participant and public involvement

2.10.2

As a consortium undertaking a secondary analysis of four separate studies, IMiC will not directly engage participants or the public in study design, conduct and reporting. However, each study followed their own protocols locally regarding engagement, and study representatives were encouraged to bring these perspectives to IMiC discussions. Moreover, we plan to communicate IMiC research results to the public and participants through each study’s local team.

## Discussion

3

Taking a collaborative, multi-disciplinary and multi-omic approach to HM science, IMiC will provide new insights on the sources and consequences of the tremendous variation in human milk composition across populations. These findings will fill gaps (7–9) and advance knowledge about how HM operates as a biological system to support infant development, and identify known and novel HM components and “profiles” that could be leveraged to develop new approaches to optimizing infant nutrition and growth in diverse settings.

### Analytical innovations

3.1

While there is an increasing appreciation for the need to study HM as a biological system (6, 44), this concept is still relatively new and few studies have taken this approach. The IMiC team is rising to the challenge and promises to deliver innovative approaches and novel findings. By measuring and integrating a broad collection of HM components, and applying advanced machine learning techniques, we will have unprecedented opportunities to infer and investigate biological pathways and mechanisms. By including exploratory assays, we have the potential to discover new HM components relevant to infant growth. By analyzing HM from maternal nutritional intervention studies, we can determine if HM mediates the impact of these interventions on infant growth—if so, we can pinpoint which component(s) are responsible.

### Challenges

3.2

General challenges for the IMiC consortium include: (1) the administrative burden and complexity of financial and legal agreements for subgrants, data sharing and/or material transfer across 13 institutions; (2) the logistical burden and complexity of shipping frozen human milk across countries and continents; (3) communication challenges related to geographic and cultural diversity; (4) data harmonization challenges stemming from the different study designs and data collection time points; and (5) ensuring equitable representation, participation, collaboration and attribution for all members, including those from low-middle-resource and low-middle-income country (LMIC) settings. The latter has been the primary focus of the IMiC LMIC working group, whose work will be described elsewhere.

Selection bias and generalizability are challenges of particular note in our study, where participants were selected partially based on data availability across independent studies across diverse settings. For instance, only participants able to provide milk samples and attend follow-up visits for infant anthropometric measurements could be included, and unmeasured maternal or socioeconomic factors could differ between those able to participate and all eligible participants, leading to potential biases in the associations identified (98). We will implement strategies to mitigate selection bias during the data analysis phase (e.g., through careful consideration of handling missing data) and will consider its unintended effects during the knowledge translation phase, such as lack of transferability of some conclusions across geographic settings. We will also be sure to use the most relevant reference standards for the diverse populations we are studying (e.g., using mid upper arm circumference rather than BMI to identify maternal undernutrition, and using international infant growth standards that have been validated across different ethnic groups).

Additionally, the overall IMiC project was delayed by approximately 18 months due to the COVID-19 pandemic. Two studies (MISAME and VITAL) were also delayed in completing their recruitment and data collection, several analytical laboratories were shut down, and supply-chain disruptions affected the availability of materials and reagents. The individual studies participating in IMiC each faced distinct challenges that are beyond the scope of this paper (e.g., recruiting and standardizing protocols across multiple towns or provinces; logistical challenges in low-middle-resource settings related to collecting samples, maintaining cold chain, receiving shipments and resolving taxation issues).

